## Study Arms

### Intervention Condition

The intervention will consist of (1) availability of the adapted e-mhGAP-IG for use on a clinic tablet, (2) participation in remote supervision and the support module developed in phase 1 for implementation in Nepal and Nigeria, and (3) training to all relevant PCWs and supervisors in the use of the adapted e-mhGAP-IG and clinical dashboard. Health care providers with enhanced mental health knowledge who have attended the training of trainers workshops for the e-mhGAP-IG and remote supervision will act as supervisors for the purpose of the study. These might include, but are not limited to, psychiatrists, mental health nurses, general physicians, senior PCWs, and counselors.

### Control Condition

The control condition will consist of (1) availability of the paper version of the mhGAP-IG v2.0 adapted for use in Nepal and Nigeria, (2) participation in remote supervision and the support module developed in phase 1 for implementation in Nepal and Nigeria, and (3) training to all relevant PCWs and supervisors in the use of the paper version of the mhGAP-IG v2.0 and supervision from distance ([Table 1](#)). Trained specialists in the research teams within each study site will act as supervisors for the purpose of the study. Supervisors are intended to be health care providers with enhanced mental health knowledge who have attended the training of trainers workshops for the paper mhGAP-IG v2.0. These might include, but are not limited to, psychiatrists, mental health nurses, general physicians, senior PCWs, and counselors.

Table 1.

Feasibility study arm components.

| Component                                                                              | Intervention condition | Control condition |
|----------------------------------------------------------------------------------------|------------------------|-------------------|
| e-mhGAP-IG a v2.0                                                           | ✓                      |                   |
| Paper mhGAP-IG b v2.0 c                                          | ✓                      | ✓                 |
| Remote supervision and support module                                                  | ✓                      | ✓                 |
| Primary care workers' training in use and administration of the relevant mhGAP-IG v2.0 | ✓                      | ✓                 |
| Primary care workers' training in a clinical dashboard                                 | ✓                      |                   |
| Supervisors' training in relevant mhGAP-IG and remote supervision and support          | ✓                      | ✓                 |
| Supervisors' training in a clinical dashboard                                          | ✓                      |                   |

ae-mhGAP-IG: electronic Mental Health Gap Action Programme Intervention Guide.

bmhGAP-IG: Mental Health Gap Action Programme Intervention Guide.

cThe paper mhGAP-IG v2.0 will be used in intervention condition training and will be available for use as a resource throughout the study.

## Remote Supervision

In both study arms, remote supervision will comprise an initial face-to-face meeting (where possible) and subsequent contact by voice and text messaging to discuss implementation of the mhGAP-IG (paper or e-version) and any case queries. Supervision format (eg, voice calls, video calls, messaging, group, and individual) will be agreed upon by each supervision dyad. Supervisors will be provided with training on how to set up and run supervision remotely using telephone and other common communication platforms such as WhatsApp groups before the start of the study. Training will cover issues such as building rapport, format for running supervision over a telephone, format for clinically supportive WhatsApp groups, and ensuring patient confidentiality when using remote supervision methods. PCWs will receive training on how to make the most of the remote supervision during the mhGAP-IG training. PCWs will have access to project mobile phones to facilitate remote supervision. Both PCWs and supervisors will be provided with data packages.

## Randomization and Allocation Concealment

Clinics will be randomized to the control or intervention conditions, with equal number of clinics in either group (1:1). Randomization will be carried out independently (to ensure concealment) by the trial statistician via a computer-generated random sequence before participants are recruited or the intervention is initiated. PCW selection will be performed according to health staffing levels before randomization of clinics to a study arm. Blinding or masking of participants, clinicians, and fieldworkers will not be possible, as it will be clear which conditions clinics or municipalities are assigned to during implementation and data collection. However, the senior and junior trial statisticians who carry out the randomization will not know the characteristics of the clinics being randomized, and the primary statistical analysis will also be blinded to allocation status.

## Statistical Power and Sample Size Calculation

The study will take place in 1 government administrative region in Nepal and 4 in Nigeria. We will identify approximately 20 PHCs in Nepal and 6 in Nigeria. In each country, half of the PHCs will be randomly allocated to either the e-version or the paper version of the mhGAP-IG. As the clinics vary in size, we will assess at least two staff members in each clinic, with an estimated 2-5 health workers per facility and an overall enrollment of 40 PCWs in Nepal and 30 PCWs in Nigeria. Regarding patient numbers, on the basis of the sample size for the study by Sangha et al [34] on smartphone app for improving cognition to improve case detection, we will conduct within-arm comparison detection rates if at least 40 patients screen positive on the Patient Health Questionnaire (PHQ-9) in the research assistant interview in the 1-month pretraining period and in the first month of the posttraining patient enrollment period, which begins after 3 months of intensive supervision. This will allow us to detect a within-arm increase in the clinical case identification rate of 43% for the e-mhGAP-IG after the implementation of the e-version with 90% power at the 5% level of significance, assuming an intraclass correlation coefficient of 0.02. For example, with a 10% detection rate pretraining, 2 patients would receive a health worker depression diagnosis out of 20 patients screening positive. After training, the detection rate would increase to 53%, which equates to 11 patients diagnosed by a health worker out of 20 patients screening positive.

## Data Collection

### Overview

In line with the current best practice in implementation research [32], the research team will evaluate implementation processes and outcomes (eg, acceptability and feasibility) and factors that influence effectiveness implementation (eg, organizational readiness to change) across multiple stakeholder groups, including patients, PCWs, and supervisors, and at different stages of implementation [32,35]. This offers a 360-degree implementation evaluation, which considers the needs and perspectives that typically differ between stakeholder groups and can vary over time. Data collection procedures are outlined in [Figure 1](#).

### Implementation Data

#### PCWs Data

PCWs will be interviewed by a member of the research team during a 1-week period at each PHC clinic at 4 time points: (1) before mhGAP-IG training, (2) immediately post training, (3) 3 months post training, and (4) 8 months post training. During the research interviews, all PCWs will complete quantitative assessments, assessing 6 variables related to the implementation of the intervention:

1. Implementation readiness: Health workers' resolve and capability to implement the e-mhGAP-IG (ie, readiness to change) will be assessed using the Organizational Readiness for Implementing Change (ORIC) scale [36]. ORIC is a 12-item, theory-based measure assessing health workers' commitment toward and ability to implement change.
2. Acceptability, appropriateness, and feasibility: Acceptability, appropriateness, and feasibility of the mhGAP-IG and remote supervision will be assessed using the Acceptability of Intervention Measure (AIM), Intervention Appropriateness Measure (IAM), and Feasibility of Intervention Measure (FIM), respectively [37]. These brief, 4-item instruments have been developed by implementation scientists and mental health professionals and display good psychometric properties. Cultural and linguistic adaptation and further psychometric evaluation will be undertaken before the deployment of the measures in this study. The appropriateness, feasibility, and acceptability of the mhGAP-IG and remote supervision will also be assessed through qualitative interviews with health workers at the last data collection time point (PCW3).
3. Fidelity: Patient records and app use, as recorded electronically through the e-mhGAP-IG v2.0, or patient records, as recorded on paper in clinics randomized to provide the paper version mhGAP-IG v2.0 and supervision notes, will be assessed by members of the research team to determine fidelity to the training manuals for the paper mhGAP-IG v2.0 and the adapted e-mhGAP-IG v2.0.
4. Adoption: Health workers' intention to adopt mhGAP-IG will be assessed by using 2 study-specific questions regarding provider-intended use within the study and after the study has ended. Intention to adopt at the provider level will also be assessed through qualitative interviews with health workers.
5. Integration and sustainability: The potential for long-term integration of the mhGAP-IG v2.0 within standard health services will be assessed using the NoMAD (Normalization Measure Development) scale [38,39]. NoMAD is a 23-item instrument that assesses staff perceptions of factors relevant to embedding interventions in health care. NoMAD consists of 4 theoretical constructs: (1) coherence, (2) collective action, (3) cognitive participation, and (4) reflexive monitoring.
6. Operating costs: The time taken to be trained and to use the paper and electronic tools and for remote supervision will be estimated from information collected from staff, and this, combined with information on staff wages, will be used to derive operating costs for the economic modeling.

During the last data collection time point (PCW3), 15 PCWs in each country will be randomly selected and invited to participate in an additional qualitative interview with a member of the research team to gain further insight into their views on the implementation of the mhGAP-IG v2.0

and remote supervision. We will aim to conduct focus group discussions (FGDs) in the first instance. However, where this is not possible, individual interviews will be conducted. Individual interviews and FGDs will be audio recorded and last no longer than 30 and 60 minutes, respectively. The interviews will be transcribed and anonymized before analysis.

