On the basis of prior data on primary care service use and screening depression rates, we anticipate being able to screen approximately 50% of adult patients presenting to primary care, with a possibility of screening a higher percentage depending on patient flow in the facility [33]. Therefore, we anticipate screening approximately 200 patients per arm per country per month (ie, 400 patients per country in the 1-month pretraining patient enrollment period and 1200 patients per country in the 3-month posttraining patient enrollment period).

Inclusion criteria for patients to be screened include the following:

- Attending PHC for treatment of a new case at recruitment
- Reached the age of adulthood (ie,  $\geq 18$  years)
- Fluent in Nepali (Nepal only) or English or Yoruba (Nigeria only).

Adult attendees will be deemed ineligible for the study if they are unable to understand or complete study assessment (eg, individuals with severe learning disability or dementia), unable to provide informed consent, or have a medical emergency requiring immediate intervention.

All patients who meet the eligibility criteria and choose to enroll in the study will then be screened by a research assistant to determine their depression status. Following this screening, patients will be evaluated by a PCW who will make an independent diagnosis without speaking to the research assistant or reviewing the screening results. Administration of screening tools may occur before or after the patient meets the health worker based on the workflow of the clinics. After patients meet the PCWs, a research assistant will review the provider's case notes to document whether or not a depression diagnosis was made.

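### Adoption of the e-mhGAP-IG is measured only as stated intention although paper stays available in intervention clinics, and paper records there are not a named fidelity source

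*Protocol*

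**What the plan says.** Four statements in the protocol bear on this.

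- **Adoption as an outcome.** The Abstract (Methods) lists adoption of the e-mhGAP-IG, specifically the electronic guide, among the secondary implementation outcomes.
- **How adoption is measured.** Implementation Data, PCWs Data, item 4: "intention to adopt mhGAP-IG will be assessed by using 2 study-specific questions regarding provider-intended use", covering the study period and the time after it. The qualitative part has the same target: "Intention to adopt at the provider level will also be assessed through qualitative interviews with health workers".
- **Paper in the intervention arm.** Table 1 ticks the paper guide for both arms, and footnote c states: "The paper mhGAP-IG v2.0 will be used in intervention condition training and will be available for use as a resource throughout the study".
- **How fidelity is measured.** PCWs Data, item 3, names two sets of sources: "Patient records and app use, as recorded electronically through the e-mhGAP-IG v2.0, or patient records, as recorded on paper in clinics randomized to provide" (meaning control clinics). Supervision notes are listed as well. Fidelity is judged against the training manual of each version.

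Two other places touch on use of the app. PCW and Patient Outcome Analysis mentions penetration once, without a numerator, denominator or source. Participants has a research assistant review each screened patient's "case notes to document whether or not a depression diagnosis was made", which does not record the guide used.

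**The concern.** In a feasibility trial of an app, a basic question is whether trained staff use the app when the paper guide is also within reach. The protocol names that question as an outcome but answers it with intentions. The items are also described as being about mhGAP-IG, which exists in both formats in an intervention clinic. A worker who has put the tablet aside and uses the paper guide could truthfully state a strong intention to use mhGAP-IG.

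The fidelity sources leave a related gap. If a worker in an e-version clinic manages a patient from paper, the app holds no record of that visit, and the paper notes are not listed as something to be scored there. The fidelity result would then describe only patients for whom the app was used.

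The future trial would be planned on these results. None of the listed progression criteria concerns app use, fidelity or adoption, so nothing else in the plan would flag a return to paper.

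**Working it through.** The protocol gives no figure for switching, adherence or uptake, so there is no stated figure to reproduce. The check is a comparison of the text, followed by an illustration with assumed values.

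**1. Outcome against measure.** The outcome is adoption of the electronic guide. Both measures, the two questions and the interviews, are of intention, and the questions are described as concerning mhGAP-IG. Neither observes use.

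**2. Is use observed elsewhere?** App use is recorded and enters fidelity under item 3. That yields counts. To become an uptake rate, a count needs a denominator of patients with whom the app should have been used, and no section sets one. Penetration might have been meant for this but is not defined.

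**3. Could a denominator be built from data already collected?** Yes. Research assistants already document, for each screened patient, the PHQ-9 result and whether the PCW diagnosed depression. Linking that list to the app's patient-mode records gives the rate.

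**4. What could unscored paper patients do to fidelity?** Let *s* be the share of eligible intervention-arm patients managed on paper, *f_e* the fidelity among app records and *f_p* the fidelity among paper-managed patients. All three are assumptions.

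- App-record fidelity = *f_e*
- All-patient fidelity = (1 − *s*) × *f_e* + *s* × *f_p*
- Difference (app-record minus all-patient) = *s* × (*f_e* − *f_p*)

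For fidelity to the e-version itself, a paper-managed patient counts as not delivered, so *f_p* = 0. For adherence to guide content in either format, *f_p* can take any value.

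| *f_e* | *f_p* | *s* = 10% | *s* = 25% | *s* = 50% |
|---|---|---|---|---|
| 0.80 | 0 | 0.72 (+0.08) | 0.60 (+0.20) | 0.40 (+0.40) |
| 0.80 | 0.40 | 0.76 (+0.04) | 0.70 (+0.10) | 0.60 (+0.20) |
| 0.80 | 0.80 | 0.80 (0) | 0.80 (0) | 0.80 (0) |
| 0.60 | 0.80 | 0.62 (−0.02) | 0.65 (−0.05) | 0.70 (−0.10) |

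Cells show all-patient fidelity, with the difference in brackets. Example: 0.75 × 0.80 + 0.25 × 0.40 = 0.70, and 0.80 − 0.70 = 0.10.

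For e-version fidelity (first row) the app-record figure can only equal or exceed the all-patient figure. For content the sign depends on whether adherence is better in the app or on paper. With *s* = 0 every difference is zero.

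**5. Uptake in the same scenarios.** If every patient not managed in the app is managed on paper, observed uptake is 1 − *s*: 90%, 75% and 50%. The intention items are not calculated from *s* and need not move with it.

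**The case against.** The strongest reply is that item 3 lists app use and supervision notes alongside patient records. A clinic that stopped opening the app would show low app use, so the inference that it would score high on fidelity does not follow from the text. This stands. What remains is narrower: counts without a denominator show that use is low but not what fraction of eligible patients were reached, and supervision notes may reveal switching without giving a rate.

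Second, a reader might infer that control clinics are scored on all their paper records, making the comparison between arms biased. The documents do not support that. Item 3 lists sources; it sets no sample or denominator for either arm, and the analysis sections specify no between-arm contrast of fidelity. Study Design speaks only in general terms of comparing implementation outcomes.

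Third, a reader might state as fact that uptake and fidelity are overstated. Footnote c makes paper available as a resource; it does not say that staff will manage patients from it instead. Switching is a possibility, its extent is unknown, and for guide content the direction may reverse.

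Fourth, definitions of penetration and fidelity scoring may properly sit in an analysis plan or a fidelity manual. This is fair for the definitions. It does not settle which records are collected and scored, or the choice to measure adoption by intention; those are fixed in the protocol.

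Finally, NoMAD and the interviews add information on integration into practice. They report perceptions, not use, and so do not fill the gap.

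**Conclusion.** The point holds in a limited form. It is firm that adoption of the e-mhGAP-IG, a named secondary implementation outcome, is measured only by stated intention while paper remains available in the same clinics, and that no uptake rate over eligible patients is defined. High reported adoption is therefore compatible with little use of the app.

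It is conditional that e-version fidelity may be overstated: this requires that some patients are managed on paper and that their notes go unscored. The illustrative differences rest wholly on assumed paper shares and adherence values and are not estimates for this trial.

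A reader might also infer that paper-managed patients are lost from the detection outcome. They are not: detection uses the PHQ-9 and the clinical notes of screened patients, whichever guide was used. Nor do the stated progression criteria use fidelity or adoption. The point is a worthwhile and inexpensive improvement in measurement, and does not threaten the trial's primary outcomes of feasibility and acceptability.

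**What to change.** **Item 4 (adoption).** In e-version clinics, report observed use:

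- the proportion of enrolled patients with a PCW depression diagnosis in the case notes who have an app patient-mode record;
- the same proportion among PHQ-9 screen-positive patients, a denominator that does not depend on the PCW's diagnosis;
- the proportion of trained PCWs using the app in each month.

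Keep the intention questions and interviews as supportive. The two patient denominators should be read together, since a low figure among screen-positive patients mixes non-use of the app with non-recognition of depression. A missing app record shows that the app was not used for that patient; it does not by itself show that the paper guide was.

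**Item 3 (fidelity).** Add paper patient records in e-version clinics as a source where no app record exists, and report fidelity with and without those patients. Keep any between-arm comparison of fidelity descriptive, because patients diagnosed by a PCW are a group formed after randomization by the very behaviour that the guide is meant to change.

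**Cost.** Protocol wording, linkage of app logs to the case-note list, and scoring of some additional paper notes in intervention clinics. Reported e-version adoption and fidelity may come out lower.

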#### Supervisor Data

mhGAP-IG supervisors will be interviewed by a member of the research team during a 1-week period at 2 time points: (1) immediately post training and (2) 8 months post training ([Figure 1](#)). Interviews will focus on perceived acceptability, appropriateness, and feasibility of remote supervision using the quantitative assessments described above (ie, AIM, IAM, and FIM). All supervisors will be invited to participate in a qualitative interview 8 months post training to gain further insight into their experiences of remote supervision. FGDs will be conducted where possible, with the remaining selected participants completing individual interviews. All qualitative interviews will be audio recorded and last between 30 minutes for individual interviews and 60 minutes for FGDs. The interviews will be transcribed and anonymized before analysis.

#### Patient Data

We estimate screening a minimum of 400 patients at each site during the pretraining enrollment period and 1200 patients in the posttraining enrollment period (starting 3 months after the mhGAP-IG training). In the posttraining period, we will include a subset of patients who have received a health worker depression diagnosis to follow-up for treatment outcomes. We will follow up with them at approximately 3 months after they are screened to measure their treatment outcomes. A subset of patients will also participate in FGDs to assess their perspectives on the acceptability (AIM) and appropriateness (IAM) of the intervention 3 months after their baseline health care appointment.

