5. Suicidal ideation and behavior: Suicidal ideation and behavior will be assessed, in Nepal only, using suicidality questions adapted from the Composite International Diagnostic Interview suicidality module [57]. This tool has been widely used in Nepal [58]. We will ask participants whether they had thought of taking their own life in the past 12 months. Those who will respond affirmatively to the ideation question will be asked if they had made a plan to take their own life. In Nepal, those who meet the criteria for current suicidal thoughts or those who attempted suicide in the past 3 months will be immediately referred to a trained psychosocial counselor. In Nigeria, patients endorsing the suicidal ideation item from the PHQ-9 will receive further assessment of suicide risk in line with local protocols.

Confirmation of diagnosis and treatment initiation will be collected from the clinical notes by PCWs. Patients interviewed in the first 3 months of data collection and who screen positive for depression will be invited to participate in a follow-up interview 3 months after their first appointment. The interview will consist of quantitative assessments of depression (PHQ-9), disability (WHODAS 2.0), therapeutic alliance (the ENACT-service user version), and suicide ideation and action Composite International Diagnostic Interview. Treatment details will be extracted by the research team from patient records to document treatment retention.

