#### PCW and Patient Outcome Analysis

The primary outcome will be the accuracy of the depression diagnosis. The research team will identify a patient as screening positive based on the PHQ-9 result immediately before or after the patient sees the PCW. *Screening positive* will be defined as scoring  $\geq 10$  on the PHQ-9. The research team will also assess sensitivity to change, for change in both the PHQ-9 and WHODAS 2.0 scores from baseline and 3 months after initiation of treatment. *Positive diagnosis* will be defined as a clinical diagnosis of depression documented by the health worker in the clinical notes. *Accurate detection* will be defined as PHQ-9  $\geq 10$  and a health worker depression clinical diagnosis. We will also report findings in terms of the sensitivity and specificity of health worker diagnoses. *Sensitivity* will be defined as the proportion of health worker–diagnosed patients who had PHQ-9 above the cutoff, out of all patients who scored above the PHQ-9 cutoff. *Specificity* will be defined as the proportion of patients who did not receive a health worker depression diagnosis and scored below the PHQ-9 cutoff, out of all patients scoring below the PHQ-9 cutoff.

Features of the cRCT design will be accommodated in all analyses, and an intention-to-treat approach will be used. The principles of analysis will be (1) the PHC-level accuracy outcome is binomial (ie, number of accurate diagnoses out of all diagnoses based on patient-level data), and therefore, a generalized linear mixed model will be used (specifically, a log-binomial regression to obtain probability ratios); (2) accuracy is a cumulative measure, and therefore, there are no repeated measures over time; and (3) missing data can occur at either the health worker or patient level.

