Differences in detection rates will be assessed using patient outcome data at 3 months after enrollment, only in depression cases identified in each arm (ie, scoring  $\geq 10$  on the PHQ-9), and the health worker clinical diagnosis. A 3-level hierarchical model will be used when all time points will be included as repeated measures in the model to improve power and take into account clustering of the observation at patient and PHC levels. The 3-level linear mixed model will be used to estimate a 95% CI for the comparison of clinical diagnosis and PHQ-9 screening positive rates (as well as a subanalysis with PHQ-9 plus WHODAS 2.0 criteria) within electronic and paper mhGAP-IG versions. Secondary outcomes (eg, knowledge and attitudes) will be assessed within each arm with a similar methodology for the primary outcomes, using generalized linear mixed models depending on the type of outcome (normal, binary, and count). Clinical feasibility will also be triangulated using penetration and costing data.

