### Health Economic Analysis

We will develop a simulation model to assess the potential cost-effectiveness of the e-mhGAP-IG compared with the paper-based tool. We are not measuring patient outcomes within the study; hence, costs of services and impacts on patients will be taken from other sources. The model will take the form of a decision tree that maps out key events following the use of either tool and outcomes that are achieved. A simple form of the model will have cases detected or not as key events and whether or not outcomes improve as a result of detection (the latter information coming from previous research). The cost of providing care for people detected will be included as will the reduction in disability-adjusted life years (DALYs) following treatment. Some of the data will be obtained from within the study (costs of using the tools based on staff time and rate of detection of depression), whereas other data (costs of treatment and DALYs) will be obtained from the wider literature and expert opinion. The model will be subject to sensitivity analyses to address the uncertainty of the model parameters. The model will enable us to generate a cost per DALY avoided by using the tool.

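### The protocol defines the 3-month patient follow-up cohort in two incompatible ways, and one of them selects on a health worker diagnosis made after randomisation

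*Protocol*

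**What the plan says.** Two sections of the Protocol are headed Patient Data, and each describes who is followed to 3 months.

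- **Patient Data under Implementation Data:** in the post-training period "we will include a subset of patients who have received a health worker depression diagnosis to follow-up for treatment outcomes". On timing: "We will follow up with them at approximately 3 months after they are screened to measure their treatment outcomes".
- **Patient Data under Outcome Data:** for patients seen during the opening 3 months of fieldwork, those "who screen positive for depression will be invited to participate in a follow-up interview 3 months after their first appointment".

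PCW and Patient Outcome Analysis defines the two terms separately. On screening: "The research team will identify a patient as screening positive based on the PHQ-9 result", with a cutoff of 10 or more. A positive diagnosis "will be defined as a clinical diagnosis of depression documented by the health worker in the clinical notes". The same section describes change in PHQ-9 and WHODAS 2.0 "scores from baseline and 3 months after initiation of treatment".

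Objective 6 is to describe depression treatment outcomes, and Study Design says that clinical outcomes of the electronic and paper versions will be compared. Health Economic Analysis nevertheless states: "We are not measuring patient outcomes within the study".

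**The concern.** Staff inviting patients to the 3-month interview cannot follow both rules. The first leaves out patients who screen positive but are not diagnosed, and admits patients who are diagnosed but score below 10. The second does the reverse.

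The two rules also differ statistically. The research team's PHQ-9 is scored independently of the health worker. The health worker's diagnosis comes after clinics are randomised, and its accuracy is the outcome intended for the full trial. A cohort chosen on it is conditioned on something the intervention may alter. If one arm detects more cases and severe cases are easier to detect, the diagnosed patients in that arm are milder on average, even when treatment has no effect.

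Three things are at stake: the meaning of the treatment-outcome description carried into the full trial, any between-arm reading of clinical outcomes, and the denominator of the patient-retention criterion for progression. Undetected cases who are not invited at the time cannot be recovered at analysis.

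**Working it through.** **1. The definitions side by side**

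| | Implementation Data rule | Outcome Data rule |
|---|---|---|
| Entry condition | Health worker diagnosis | PHQ-9 ≥10 |
| PHQ-9 ≥10, not diagnosed | Out | In |
| PHQ-9 <10, diagnosed | In | Out |
| Time origin | Screening | First appointment |

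The Figure 1 legend (Study Design) also counts the 3 months from the baseline appointment. Screening and appointment fall on the same visit, so these three agree in substance. Only the outcome-analysis section counts from treatment initiation, and that origin does not exist for an undetected case.

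**2. Share of screen-positive patients affected**

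Statistical Power and Sample Size Calculation uses an illustrative post-training detection rate of 53%. The share of screen-positive patients outside a diagnosed-only cohort is 1 − 0.53 = 47%.

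**3. Numbers per arm**

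Participants gives 200 screened per arm per country per month, so 3 × 200 = 600 over the 3-month post-training period. Settings gives depression prevalence of 16.8% (Nepal, primary care) and 5.5% (Nigeria, not stated to be a primary care figure). Taking these as screen-positive rates, which is an assumption:

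- Nepal: 600 × 0.168 = 101 screen-positive; × 0.53 = 53 diagnosed; about 47 not diagnosed.
- Nigeria: 600 × 0.055 = 33 screen-positive; × 0.53 = 17 diagnosed; about 16 not diagnosed.

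If 16.8% is instead true prevalence, the sensitivity (94%) and specificity (80%) that the protocol quotes for Nepal give 0.168 × 0.94 + 0.832 × 0.20 = 32.4% screening positive, about 195 per arm. The Nepal count is therefore roughly 101 to 195.

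Diagnosed patients below the cutoff would be added to the first cohort. With an assumed health worker specificity of 95%, that is (600 − 101) × 0.05 ≈ 25 per arm in Nepal and (600 − 33) × 0.05 ≈ 28 in Nigeria.

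**4. Effect on the retention criterion**

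The 95% half-width around 67% retention, ignoring clustering, is 1.96 × √(0.67 × 0.33 / n). It is about 9 points at n = 101, 13 at n = 53, 16 at n = 33 and 22 at n = 17. The last figure in each country counts only screen-positive members of the diagnosed cohort. The two rules also measure retention in different people.

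**5. Illustration of the case-mix shift**

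Suppose the arms detect 53% and 30% (the 30% is assumed), with identical patients and no treatment effect.

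- *Normal selection model.* Gap in mean baseline PHQ-9 of the diagnosed = r × SD × [i(0.30) − i(0.53)], where i(p) = φ(z)/p, giving 1.159 and 0.751. With assumed SD 4: r = 0.3 gives 0.49, r = 0.5 gives 0.82, r = 0.7 gives 1.14 points.
- *Logistic detection.* With PHQ-9 assumed normal (mean 14, SD 3.5) and truncated to 10–27, a log-odds slope of 0.2 per point gives 0.42 and a slope of 0.4 gives 0.77 points.
- *Null cases.* The gap is zero if detection is unrelated to severity, or if detection depends on severity in the same way and is equally frequent in both arms.

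The range is about 0.4 to 1.1 points, and it concerns baseline score, not change.

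**The case against.** A reader might infer that the diagnosed-only rule biases every comparison of treatment outcomes. The document does not support that. Both arms receive mhGAP training, remote supervision and the paper guide (Table 1), and no section states an expected between-arm difference in detection. The 10% and 53% rates are before and after training within an arm, so 10% should not be applied to a cohort followed only after training.

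The planned use is also mostly not comparative. Objective 6 is descriptive, Participants speaks of descriptive information, and the analysis section works within each arm. Only the general sentence in Study Design promises to compare clinical outcomes. Following diagnosed patients is a legitimate way to describe people who were treated. Baseline PHQ-9 is recorded, so imbalance on it would be visible and could be adjusted for.

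Two further inferences should be resisted.

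- The phrase "only in depression cases identified in each arm", followed by a mention of the clinical diagnosis, could be read as a third cohort requiring both conditions. That sentence is about detection rates, so it does not clearly define the treatment-outcome population.
- One might say the economic model is deprived of an input. It is not: the model takes outcome improvement and DALYs from external sources by design.

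These points limit the bias argument. They do not remove the contradiction: a descriptive estimate and a retention rate each need one defined cohort.

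**Conclusion.** The two Patient Data sections are incompatible as written, and the time origin in the outcome analysis cannot be applied to undetected cases. The statement that patient outcomes are not measured, taken literally, conflicts with objective 6 and with the planned 3-month PHQ-9 and WHODAS 2.0.

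At the protocol's 53% detection rate, 47% of screen-positive patients depend on which rule is followed. The counts per arm rest on treating the quoted prevalences as screen-positive rates.

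The bias is conditional. It needs detection to differ between arms and to be related to severity, and neither its size nor its occurrence can be established from the document. The 0.4 to 1.1 point gap is only an illustration.

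This is a feasibility trial with a descriptive treatment-outcome objective, so the point should be fixed but does not undermine the primary feasibility aims.

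**What to change.** - **One cohort.** In both Patient Data sections, state that all post-training patients with PHQ-9 ≥10, or a random sample of them, are invited to the 3-month interview whether or not the health worker diagnosed depression.
- **One time origin.** Use 3 months after the index visit throughout, and replace the treatment-initiation wording in PCW and Patient Outcome Analysis.
- **Diagnosed patients as a subgroup.** Report them descriptively.
- **Retention.** Use the same cohort as the denominator of the 67% patient criterion.
- **Health Economic Analysis.** Say that 3-month PHQ-9 and WHODAS 2.0 are collected, but that the model takes its outcome effects from external sources. Do not feed observed change by detection status into the model: detected and undetected patients are not randomised groups, and the contrast is confounded by severity.

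The cost is wording, plus more 3-month interviews of screen-positive patients than a diagnosed-only cohort would need: at 53% detection, up to about 47 more per arm in Nepal and 16 in Nigeria on the counts above, and more in Nepal if the screen-positive rate is higher. The Outcome Data section already promises these interviews, and random sampling can cap them. The wider cohort does not remove other risks, such as unblinded fieldworkers and loss to follow-up.
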